## Abstract

**Background:**

Inherited cystic kidney disease is a spectrum of disorders in which clusters of renal cysts develop as the result of genetic mutation. The exact methods and pipelines for defining genetic mutations of inherited cystic kidney disease are not clear at this point. This 3-year, prospective, multicenter, cohort study was designed to set up a cohort of Korean patients with inherited cystic kidney disease, establish a customized genetic analysis pipeline for each disease subtype, and identify modifying genes associated with the severity of the disease phenotype.

**Methods/design:**

From May 2020 to May 2022, we aim to recruit 800 patients and their family members to identify pathogenic mutations. Patients with more than 3 renal cysts in both kidneys are eligible to be enrolled. Cases of simple renal cysts and acquired cystic kidney disease that involve cyst formation as the result of renal failure will be excluded from this study. Demographic, laboratory, and imaging data as well as family pedigree will be collected at baseline. Renal function and changes in total kidney volume will be monitored during the follow-up period. Genetic identification of each case of inherited cystic kidney disease will be performed using a targeted gene panel of cystogenesis-related genes, whole exome sequencing (WES) and/or family segregation studies. Genotype-phenotype correlation analysis will be performed to elucidate the genetic effect on the severity of the disease phenotype.

**Discussion:**

This is the first nationwide cohort study on patients with inherited cystic kidney disease in Korea. We will build a multicenter cohort to describe the clinical characteristics of Korean patients with inherited cystic kidney disease, elucidate the genotype of each disease, and demonstrate the genetic effects on the severity of the disease phenotype.

**Trial registration:**

This cohort study was retrospectively registered at the Clinical Research Information Service (KCT0005580) operated by the Korean Center for Disease Control and Prevention on November 5th, 2020.

## Background

Inherited cystic kidney disease (iCKD) is a hereditary disorder in which clusters of cysts develop within the kidneys [1, 2]. Approximately 100 genes involved in renal cystogenesis are known to result in dysfunction of a hair-like organelle called the cilium [3]. Therefore, iCKD is otherwise called ciliopathy [4, 5]. iCKD encompasses autosomal-dominant polycystic kidney disease (ADPKD), tuberous sclerosis complex [6], von Hippel-Lindau disease, autosomal-dominant tubulointerstitial kidney disease (ADTKD) [7], and pediatric diseases such as autosomal recessive polycystic kidney disease (ARPKD) [8] and nephronophthisis (NPHP) [9]. There are still many other disorders in which causative mutations have not been found by molecular diagnosis.

Although iCKDs are caused by genetic derangement, most are diagnosed by clinical impressions other than molecular diagnosis. However, clinical diagnosis is not always easy because iCKDs often share common clinical manifestations. Therefore, genetic testing is important to establish a correct diagnosis and treatment. A recent report by Bullich et al. demonstrated that they could confirm diagnosis in 32% of cases with unspecified clinical diagnosis by establishing a kidney gene panel [10]. They also showed that genetic testing changed the clinical diagnosis in 2% of cases. Therefore, genetic testing should be the most important venue to confirm diagnosis and establish precision medicine.

Moreover, the exact methods and pipelines to find genetic mutations in iCKDs are not clear at this point. It may be reasonable to perform targeted exome sequencing or Sanger sequencing of *PKD1* and *PKD2* to define pathogenic mutations in well-known clinical phenotypes such as ADPKD. However, our previous study demonstrated that approximately 20% of patients with typical ADPKD did not reveal causative germline mutations by targeted exome sequencing of *PKD1* and *PKD2* [11]. In addition, extrarenal manifestations often do not follow renal manifestations. For example, the severity of polycystic liver accompanying ADPKD does not always correlate with the severity of renal disease [12]. Therefore, modifying genetic effects or gene dosage effects may play a role in determining the severity of renal and extrarenal phenotypes in ADPKD [13]. In addition, apart from typical ADPKD, there are patients with atypical polycystic kidney disease who either do not show concordant features within the family, do not have typical imaging features of ADPKD, or have discordant disease severity between renal volume and renal function [14]. Mutations in *GANAB* and *DNAJB11* are known to cause a mild phenotype of polycystic kidney and liver disease [15, 16]. However, the exact prevalence and prognosis of atypical polycystic kidney disease is unknown at this point. Last, iCKDs in the pediatric population are typically rare diseases, and their molecular diagnoses are even more difficult. Therefore, building a cohort of iCKDs is necessary to reveal their genetic characteristics.

Therefore, we designed a 3-year prospective, multicenter, cohort study to establish a cohort of Korean iCKD patients, establish a customized genetic analysis pipeline that can genotype each iCKD and identify the modifying genes associated with the severity of the disease phenotype.

## Methods/design

### Study design and settings

This is a 3-year prospective, multicenter, cohort study to elucidate genotype-phenotype associations among iCKD patients. A total of 11 medical centers from 9 tertiary hospitals in Korea will participate in this study. Seven centers will enroll and collect data from adult patients, and 4 centers will enroll pediatric patients. We established a research team, statistical analysis team, database team, sequencing and biobanking team, and genetic analysis team to perform this large nationwide project. The research team is composed of 26 clinicians and 15 clinical research coordinators from 11 medical centers. The role of the research team is to recruit eligible patients and collect clinical data. The statistical analysis team supports the calculation of sample size, distribution of enrollment according to iCKD subclasses, and statistical analysis. The database team collects clinical and genetic data from each patient and builds an electronic case report form to store and manage the dataset. The database team also performs imaging analysis quantitatively and qualitatively from nonenhanced computed tomography (CT) or sonography. The team for sequencing and biobanking is outsourced to Macrogen, Inc. to collect whole blood from each medical center and perform initial genetic analysis to produce sequencing data. The residual DNA samples will be prepared for biobanking after quantity and quality checks. Finally, the genetic analysis team is composed of bioinformaticians to interpret the results of sequencing data and to determine the pathogenicity of each variant.

### Study participants

A total of 800 participants are planned to be enrolled from May 19, 2019 to May 18, 2022. Patients with ≥3 renal cysts in both kidneys are eligible to be enrolled. Those who are not able to give informed consent or are pregnant will be excluded from enrollment. Cases of simple renal cysts and acquired cystic kidney disease that involve cyst formation as the result of renal failure will also be excluded from this study. However, patients with end-stage kidney disease who are receiving renal replacement therapy due to iCKD can be enrolled.

The patients will be classified into typical ADPKD, atypical polycystic kidney disease, and other iCKDs after enrollment. Typical ADPKD is defined according to Pei-Ravine criteria as previously described [17]. Atypical polycystic kidney disease is defined either when the case is typical ADPKD but the patient does not have a family history of polycystic kidney disease or when the imaging phenotype is atypical as follows: unilateral, asymmetric, segmental, lopsided, bilateral or unilateral atrophic kidneys [18]. Other iCKDs are rare disease entities in children and adolescents. The other iCKDs include but are not limited to the tuberous sclerosis complex, von Hippel-Lindau disease, ADTKD, ARPKD, *HNF-1β*-related disease and NPHP. Among the 800 participants, approximately 650 patients with typical ADPKD, 90 patients with atypical polycystic kidney disease, and 60 patients with other iCKDs will be enrolled.

The parents, siblings, or children of the enrolled patients are recommended to participate in the study by giving whole blood samples for a segregation study. We will collect family samples when genetic diagnosis is undetermined, genotype-phenotype severity is not matched, and when the extrarenal manifestation is severe. We will also collect family samples from the families with more than 3 affected individuals to define gene penetrance and modify gene effects.

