### Genetic pipeline

We will use a stepwise approach to confirm genetic diagnosis. First, we will use a targeted gene panel for the screening method. We designed a targeted gene panel (Twist Bioscience, San Francisco, CA, USA) encompassing 0.5 megabases, including 89 genes related to cystogenesis or ciliopathy as well as genes that are associated with extrarenal phenotypes such as liver cysts (Table 2). Twist technology has provided high-quality target enrichment probes to cover target genes uniformly and efficiently [25]. Targeted exon capture will be performed on genomic DNA samples using a Twist custom panel kit followed by 101 base paired-end sequencing on an Illumina NovaSeq6000 platform (Illumina, San Diego, CA, USA). Sequence reads will be aligned to the human reference genome (GRCh37/hg19) using BWA-MEM and further processed to call single nucleotide variants and indels following the GATK Best Practices workflow [26]. All variants covered by independent sequence reads with a depth of 8x or greater will be annotated with ANNOVAR. All variants will be visualized in silico to eliminate false positives. Additional genetic testing will be performed if the pathogenic mutations were not found using a targeted gene panel or if the patients have severe renal or extrarenal phenotypes compared to other family members. If the patients are clinically classified as having typical ADPKD but pathogenic mutations are not found using a targeted gene panel, the patients will undergo targeted resequencing with long-range polymerase chain reaction (PCR) combined with multiplex ligation-dependent probe amplification (MLPA) to detect large deletions. WES will take place in the following cases: 1) if the patients are clinically classified as typical ADPKD but no pathogenic mutations are found using a previous method, 2) if the patients are clinically classified as atypical polycystic kidney disease or other iCKD but pathogenic mutations are not found using a targeted gene panel, 3) if the patients present with a severe phenotype and variants cannot explain the severity, or 4) if the patients show extremely different phenotypes compared to other family members. Familial segregation analysis will also take place to define the pathogenicity of variants. A schematic representation of the genetic workflow is shown in Fig. 1.

**Table 2 Tab2:** Coverage of cystogenesis-related targeted gene panel

Target gene	Previously reported disease	Coverage
*AHI1*	Joubert syndrome	100%

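### The cyst threshold for entry differs between abstract and Methods, and typical-ADPKD cases without family history are routed past the only stated large-deletion assay

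*Protocol article*

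**What the plan says.** **Entry.** The abstract (Methods/design) states: "Patients with more than 3 renal cysts in both kidneys are eligible to be enrolled". The body (Study participants) states: "Patients with ≥3 renal cysts in both kidneys are eligible to be enrolled". Neither gives a counting unit.

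**Classes.** Study participants assigns patients, after enrolment, to typical ADPKD, atypical polycystic kidney disease or other inherited cystic kidney disease. For the first class: "Typical ADPKD is defined according to Pei-Ravine criteria as previously described". The second has two limbs. Limb 1 is clinical: "Atypical polycystic kidney disease is defined either when the case is typical ADPKD but the patient does not have a family history". Limb 2 is by imaging: "when the imaging phenotype is atypical as follows: unilateral, asymmetric, segmental, lopsided, bilateral or unilateral atrophic kidneys". The planned sizes are about 650, 90 and 60.

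**Assays.** Under Genetic pipeline, everyone starts with the targeted panel, whose workflow is described as calling single nucleotide variants and indels. Typical ADPKD without a pathogenic panel finding goes to a resequencing step built on long-range PCR, which is "combined with multiplex ligation-dependent probe amplification (MLPA) to detect large deletions", and to WES only if that also fails. In the atypical and other classes, WES follows an unrevealing panel directly, with no PCR or MLPA step in between. The Fig. 1 legend repeats this split and adds that a variant of undetermined significance (VUS) counts as unresolved at the panel step.

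**The concern.** There are two separate problems.

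1. **The main entry criterion has two versions.** The study recruits at 11 centers, and a patient with exactly 3 cysts is in or out depending on which sentence is applied. The missing counting unit matters as well. If each kidney must contain cysts, the unilateral phenotype listed under the atypical class could not be enrolled.

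2. **The class label decides which mutations can be found.** Patients whom the article itself describes as typical ADPKD move to the atypical class solely because they have no family history, and with that move they lose the long-range PCR and MLPA step. Building a genetic pipeline suited to each subtype is a stated aim. For this subgroup the stated pipeline has no step aimed at large deletions, so an unresolved case means something different from an unresolved case in typical ADPKD.

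**Working it through.** **Class sizes (Study participants).** 650 + 90 + 60 = 800, which reproduces the planned total. The atypical class is 90/800 = 11% of the cohort.

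**Entry rule, by cyst count.**

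| Cysts | Abstract (more than 3) | Study participants (3 or more) |
|---|---|---|
| 2 | not eligible | not eligible |
| 3 | not eligible | eligible |
| 4 | eligible | eligible |

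The two rules differ only at exactly 3. The number of such patients is not given.

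**Counting unit.** If the count is a total over the two kidneys, a patient with all cysts on one side can reach the threshold, and the unilateral class is consistent with entry. If the count applies to each kidney, that patient cannot enter. The text does not decide between the two.

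**Assay route after a panel result that is negative or VUS only.**

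| Class | Next step | Then |
|---|---|---|
| Typical ADPKD | long-range PCR plus MLPA | WES |
| Atypical, including typical ADPKD without family history | WES | family segregation study |

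The Genetic pipeline text and the Fig. 1 legend agree, so the split is not a slip in one sentence. No copy-number calling is stated for the panel or for WES.

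**Number affected.** Let f be the share of the 90 who are atypical through absent family history, and q the share of those without a panel diagnosis. The number affected is 90 × f × q.

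- f is not given. It is taken as 25% to 100% (assumption).
- q is not given for this class or this panel. Background reports about 20% without a causative mutation, in typical ADPKD on PKD1/PKD2 targeted exome sequencing. It is taken as 10% to 30% around that figure (assumption).

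| f | q = 10% | q = 20% | q = 30% |
|---|---|---|---|
| 25% | 2.2 | 4.5 | 6.8 |
| 50% | 4.5 | 9.0 | 13.5 |
| 100% | 9.0 | 18.0 | 27.0 |

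At the borrowed 20%, the ceiling is 90 × 1.00 × 0.20 = 18 patients. For comparison, 650 × 0.20 = 130 typical patients would go through long-range PCR plus MLPA.

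**Missed diagnoses.** These would be the number affected times the large-deletion rate. The article gives no such rate, so the product cannot be formed.

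**The case against.** **Class rules and enrolment.** A reader might infer that the class definitions also change who is enrolled. They do not: classification follows enrolment, so only the cyst wording bears on entry.

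**Overlap of the classes.** It is tempting to say that one patient is both typical and atypical. Limb 1 reads more naturally as a carve-out from typical ADPKD, and class sizes that add up to 800 suggest exclusive classes. That answers the overlap, but it fixes these patients on the WES branch, so the routing point becomes firmer.

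**The unilateral class.** This conflicts with entry only under a per-kidney count. It is an ambiguity, not a demonstrated contradiction.

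**Bias.** A reader might infer that a comparison of diagnostic yield between typical and atypical disease is biased. Genotype-phenotype correlation analysis plans no such comparison. It plans regression of kidney volume and eGFR on genotype, grouping by Mayo class and CKD stage, and modifier effects. Class-specific testing is itself an intended feature of the study.

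**Silence on WES calling.** The article does not say how WES data will be called, and a condensed article may leave that to the full protocol. This stands as a limit: the claim is that no large-deletion assay is stated for this branch, not that none will be done. It does not explain why an assay that is described, and used for the same phenotype, is withheld from these cases.

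**Size.** The 90 include patients who are atypical by imaging alone, and the 20% comes from another class and another test. Both cautions stand, so the figure of 18 is a conditional ceiling and not an estimate.

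**Conclusion.** The point holds in two parts. First, the abstract and Methods give different cyst thresholds without a counting unit, which leaves patients with exactly 3 cysts, and possibly unilateral disease, undetermined at entry. How many patients this concerns is unknown.

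Second, phenotypically typical ADPKD without family history misses the only large-deletion assay that the article states, so a negative genetic result in these patients is less complete than in typical ADPKD. The number concerned is no more than about 18, reached only if all 90 atypical patients lack a family history and the 20% figure from typical ADPKD applies. Under the wider assumptions shown it runs from about 2 to 27. No count of missed diagnoses can be supported.

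This is a modest matter for a study of 800, but it falls in a small class that the study was set up to genotype, and it is cheap to put right.

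**What to change.** 1. Reconcile the two cyst thresholds to one, and state whether the count is per kidney or a total, in a form consistent with the unilateral phenotype in the atypical class. Which threshold applies is for the investigators to decide.
2. State that the three classes are mutually exclusive, and flag typical imaging without family history as its own sub-stratum of the atypical class.
3. In Genetic pipeline and Fig. 1, route that sub-stratum's panel-negative or VUS cases through the existing long-range PCR/MLPA step before WES.

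The cost of items 1 and 2 is wording. Item 3 adds a small number of runs of an assay already in the pipeline: at most about 18 at the borrowed 20%, or 27 at an assumed 30%. Data collection at enrollment provides for DNA to be aliquoted and stored, so no new blood sample should be needed.

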### Data collection at enrollment

Demographic data, including age, sex, height and weight, will be collected. The age of diagnosis of iCKD and associated symptoms at initial diagnosis will be collected. Medical history of diabetes, hypertension, cardiovascular disease, and stroke will be investigated. Family history of iCKD, diabetes, hypertension, chronic kidney disease, dialysis, and death will be evaluated. In particular, a genetic tree will be drawn upon enrollment including 3 generations (affected and unaffected individuals). The presence of renal and extrarenal complications and their types will be recorded. Medication data, including on antihypertensive drugs and glucose-lowering therapy, will be collected. Blood pressure will be checked upon enrollment in the office. All patients will be asked to fill out the following questionnaires upon enrollment: 5 Level version of European Quality of Life 5 Dimensions questionnaire (EQ-5D-5L, adult subjects) and Pediatric Quality of Life Inventory TM (PedsQL 4.0 Generic Core Scales, pediatric subjects) to assess the quality of life of the affected patients, Patient Health Questionnaire-9 (PHQ-9) to evaluate depressive symptoms, and the modified Subjective Global Assessment (mSGA) to assess the nutritional status of the subjects.

Laboratory assessment included complete blood cell counts (white blood cells, hemoglobin, platelets), blood urea nitrogen and serum creatinine, total calcium and phosphorus, serum sodium, potassium, chloride, total carbon dioxide, total cholesterol, serum albumin, uric acid, highly sensitive C-reactive protein, urinalysis with microscopy, spot urine protein to creatinine ratio, random urine uric acid, calcium, phosphorus, sodium, potassium, chloride, and osmolality. Genetic samples will be collected once during the study period for genetic analysis. Approximately 18 mL of whole blood will be collected in 3 EDTA bottles for each adult participant, 6 mL for each family member and 4–5 mL for each child participant. The collected blood samples will be refrigerated at 4 °C until delivery to the sequencing company. The sequencing company will extract DNA from the whole blood and aliquots in several tubes to store at − 70 °C before sequencing or biobanking.

Kidney imaging will be performed at enrollment. If the patients have already undergone imaging studies within 1 year, the patients can undergo other imaging studies within a 2-year interval. Adult patients will undergo a nonenhanced kidney CT, and children and adolescents will undergo kidney sonography.

### Data collection, monitoring, and follow up

The total study scheme and annual assessment plan are depicted in Table 1. Annual laboratory assessment will be performed after enrollment for 2 years. The laboratory assessment includes the complete blood cell counts, blood urea nitrogen and serum creatinine, serum calcium and phosphorus, serum uric acid, urinalysis with microscopy, and spot urine protein to creatinine ratio. Kidney imaging will be performed every 2 years to calculate the rate of total kidney volume growth.

**Table 1 Tab1:** Study schedule

Parameter	Screen	B0	1y	2y
Informed consent	v			
Demographic information	v			
Medical history	v			
Eligibility confirmation	v			
Recent events			v	v
Medications		v	v	v
Quality of life questionnaires (EQ-5D-5L (adult), PedsQL 4.0 Generic Core Scales (pediatric))		v		
Depression assessment (PHQ-9)		v		
Nutritional assessment (mSGA)		v		
Systolic and diastolic blood pressure		v	v	v
Complete blood cell count (white blood cells, hemoglobin, platelet count, hematocrit, reticulocyte count, neutrophil count)		v	v	v
Serum calcium/phosphorus		v	v	v
Serum uric acid		v	v	v
Serum protein/albumin		v	v	v
Serum blood urea nitrogen/creatinine/estimated glomerular filtration rate		v	v	v
Plasma sodium/potassium/chloride/total carbon dioxide		v	v	v
Serum total cholesterol		v		
Highly sensitive C-reactive protein		v		
Urinalysis with microscopy		v	v	v
Spot urine protein/creatinine ratio		v	v	v
Spot urine uric acid		v		
Spot urine sodium/potassium/chloride		v		
Spot urine calcium/phosphorus		v		
Spot urine osmolality		v		
Kidney CT (adult) or abdomen sonography (pediatric)		v		

*Abbreviations*: *CT* Computed tomography, *PedsQL* Pediatric Quality of Life inventory, *PHQ-9* Patient Health Questionnaire-9, *mSGA* Modified Subjective Global Assessment

Electronic case report forms will be developed, including demographic sheets, laboratory assessments, volumetry, and genetic analysis information. The electronic case report form will be opened to the participating researchers and clinical research coordinators to fill out and modify patient information. A family tree will be drawn and stored in electronic case report form by scanning the sheet.

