### Evaluation of renal function

Renal function will be evaluated upon enrollment and every year thereafter. For the adult patients, renal function will be measured using the estimated glomerular filtration rate calculated by the Chronic Kidney Disease Epidemiology Collaboration (CKD-EPI) equation [19]. If the patients are in end-stage renal disease or receive renal replacement therapy upon enrollment, renal function will be evaluated retrospectively to calculate the renal function decline rate. For children, renal function will be measured using the estimated glomerular filtration rate calculated by the Schwartz equation [20].

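### The text and Table 1 disagree on follow-up kidney imaging: the text plans a scan every 2 years for a TKV growth rate, but the table marks imaging at baseline only

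*Protocol article*

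**What the plan says.** The section Data collection, monitoring, and follow up states the imaging plan and its purpose: "Kidney imaging will be performed every 2 years to calculate the rate of total kidney volume growth". The abstract makes the matching promise: "Renal function and changes in total kidney volume will be monitored during the follow-up period". The section Data collection at enrollment fixes the first image: "Kidney imaging will be performed at enrollment". It then adds a separate, permissive rule for patients who were already imaged in the preceding year, who may have a further study inside a two-year window.

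Table 1 is introduced with "The total study scheme and annual assessment plan are depicted in Table 1". Its columns are Screen, B0, 1y and 2y. Its last row, which begins "Kidney CT (adult) or abdomen sonography (pediatric", has a single mark, under B0. The length of follow-up comes from the same section: "Annual laboratory assessment will be performed after enrollment for 2 years".

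On height, the enrollment section says "Demographic data, including age, sex, height and weight, will be collected". Table 1 marks demographic information at Screen only and has no separate height row. It marks eGFR at B0, 1y and 2y. The section Evaluation of renal function says "For children, renal function will be measured using the estimated glomerular filtration rate calculated by the Schwartz equation".

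**The concern.** A growth rate needs at least two measurements of the same patient at different times. The text provides for them; the table does not. Follow-up lasts 2 years, so a two-yearly rule yields exactly one follow-up image, at the last scheduled visit. If that image is not taken, no other scheduled visit can supply it.

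The article names 11 centers and 15 coordinators. If some work from the table and others from the text, follow-up TKV would be missing by center and not at random. Adult and pediatric patients are enrolled at different centers, so the pattern could also follow patient type.

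**Working it through.** The plan states no figure to reproduce here. The check sets the statements side by side and counts images.

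**1. Is the blank 2y cell meaningful?** Marks in Table 1, by row:

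- B0, 1y and 2y (10 rows): medications, blood pressure, blood count, calcium/phosphorus, uric acid, protein/albumin, urea nitrogen/creatinine/eGFR, plasma electrolytes, urinalysis, urine protein/creatinine ratio.
- 1y and 2y only (1 row): recent events.
- B0 only (10 rows): quality of life, PHQ-9, mSGA, cholesterol, C-reactive protein, four further spot-urine rows, and kidney imaging.
- Screen only (4 rows): consent, demographics, medical history, eligibility.

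The table therefore separates repeated from one-off items, and 10 + 1 = 11 rows carry a 2y mark. The imaging row stands among the one-off items. The follow-up columns were not lost when the table was read.

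**2. Images and intervals per patient.** With n scheduled images, the number of intervals is n − 1. A two-point growth rate is (TKV at second image − TKV at first image) / (time between them), so it needs n − 1 ≥ 1.

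| Source | Scheduled images | n | Intervals | Growth rate |
|---|---|---|---|---|
| Table 1 | B0 | 1 | 1 − 1 = 0 | not computable |
| Text | enrollment and 2 years | 2 | 2 − 1 = 1 | computable |

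**3. Does the rule on earlier imaging settle it?** No. It is permissive, it covers only patients imaged in the year before enrollment, and it is not reflected in Table 1. It may give some patients a second image, but it is a third statement to reconcile.

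**4. Who is affected?** Planned enrollment is 650 + 90 + 60 = 800. The section Imaging analysis describes TKV measurement from nonenhanced CT, which is the adult method. For children it describes collecting sonographic images and their interpretation, without a volume measurement. The conflict over the growth rate therefore concerns mainly adults. The article gives no split of the 800 by age, so the number affected cannot be stated.

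**5. Height.** The article names the Schwartz equation but does not print it. Its dependence on height is taken here as an assumption about the standard form. Height appears only among the enrollment demographics. The article says neither that it is re-measured nor that the screening value is reused. This supports a question, not a calculation.

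**The case against.** The strongest reply is that this is one omitted mark. The text plans the repeat image and says what it is for, and the abstract agrees with it. The article says that the case report form will include volumetry. Nothing says that Table 1 overrides the text. The table also differs from the follow-up laboratory list elsewhere, since it marks albumin and electrolytes yearly and the list omits them, so it is not clearly the controlling source. TKV growth is not named as a primary outcome, and the section Genotype-phenotype correlation analysis names TKV and eGFR, not their rates of change.

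Most of this stands, and it limits the size of the point. A reader might infer that the growth rate cannot be computed at all, or that none of the 800 participants will have one. The documents do not support that: it follows only if the table is applied against the text, some patients may have earlier images, and TKV measurement is not described for children. What does not stand is the idea that the mismatch can be left alone. The article presents the table as the whole scheme, and the two statements lead to different data.

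On height, a reader might infer that follow-up eGFR in children will be biased low because an old height is reused. The article does not say so. Table 1 schedules eGFR itself at 1y and 2y without listing its inputs, and an article may leave such detail to the full protocol or case report form. No bias figure should be claimed.

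**Conclusion.** The contradiction is real and can be checked within one section. If sites follow Table 1, each patient has one scheduled image and no prospective TKV growth rate. If they follow the text, each patient who completes follow-up has two images and one interval. The consequence falls mainly on adults and depends on which source sites use, which the article does not state. Whether a stated longitudinal measure is collected should not depend on that. The height question is a minor clarification and adds nothing to the weight of the point.

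**What to change.** Reconcile Table 1 with the abstract, the enrollment imaging rule and the follow-up text, in one of two ways:

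- Table 1 shows the two-year follow-up imaging that the text already specifies, with a note on how the rule for patients imaged in the previous year fits; or
- the growth-rate statement, and the abstract's promise to monitor TKV change, are withdrawn and TKV is analysed cross-sectionally.

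Separately, add one line confirming that paediatric Schwartz eGFR at 1y and 2y uses height measured at the same visit.

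The cost is a correction to the schedule and the electronic case report form. The first option adds no imaging beyond what the text already plans. The correction should reach sites before participants pass their 2y visit, because a missed image cannot be recovered afterwards.
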